### Statistical analysis

Data will be presented using descriptive statistics, including the number of observations, means and standard deviations for continuous variables. For categorical variables, frequencies and percentages will be presented and data analysed using Chi-squared tests. Based on plotted histograms (confirming that the data may be considered as approximately normally distributed), continuous data will be analysed using a univariate general linear model (ANCOVA). In this model, treatment will be used as a categorical independent variable and baseline levels as covariates. Data will be presented as changes of means with corresponding 95% confidence intervals, standard deviations and *p*-values from group comparisons. The categorical outcome “treatment responsive” will be analysed using Chi-squared tests. A p-value below 0.05 will be considered statistically significant for all analyses. All statistical analyses will be performed by a statistician using SAS version 9.4 (SAS Institute, Cary, NC).

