### Research aims and hypothesis

The primary aim is to investigate the effects of an exercise intervention on anxiety symptoms, cognitive function, physical health and quality of life and work ability in primary care patients who fulfil criteria for anxiety disorders. A secondary aim is to analyse any potential correlation of factors in blood samples (hormones/cytokines) with anxiety symptoms and function data and to study possible dose-response effects in patients assigned to exercise of different intensities. Another secondary aim is to study mediating or moderating effects of cardiovascular fitness or other comorbidities and to analyse possible differential effects in sub-groups of participants (different initial cardiovascular fitness levels, ages and gender). In addition, health-economic analyses will be performed concerning health-related quality of life effects associated with the intervention.

Our main hypothesis is that an exercise intervention will reduce symptoms of anxiety and the number of days on sick leave, improve cognitive function and physical health variables. An additional hypothesis is that the effect will be larger for high-intensity exercise than for low-intensity.

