### Assessments

Assessments occur at baseline, post-intervention (after 12 weeks) and at one-year follow-up (Table 1). Participants will be assessed by the study physician, psychologist, psychiatrist and physiotherapist.

**Table 1 Tab1:** Measures, methods and assessment points used in the study

Variable	Measure	Method	T0 Baseline	T1 12 weeks	T2 1 year
Psychiatric diagnosis	M.I.N.I.	Interview	X	X	X
Anxiety symptoms	BAI	Self-report	X	X	X
Depression symptoms	MADRS	Self-report	X	X	X
Psychoactive drugs	Questionnaire	Self-report	X	X	X
Blood pressure	MmHg	Objective assessment	X	X	X
BMI	Kg/m^2^	Objective assessment	X	X	X
Alcohol use	AUDIT	Self-report	X	X	X
Quality of life	EQ-5D	Self-report	X	X	X
Cognitive function	WAIS-IV (d.s., b.d., m.r.)	Objective assessment	X	X	X
Cognitive function	D-KEFS (d.f.)	Objective assessment	X	X	X
Cardiovascular fitness	Åstrand’s ergometer test	Objective assessment	X	X	X
Muscle strength	One-leg-rising-test	Objective assessment	X	X	X
Sick leave	Questionnaire	Self-report	X	X	X
Hormones/cytokines	S-IGF-1, S-BDNF, S-VEGF, CRP	Blood samples	X	X	X

*M.I.N.I.* Mini International Neuropsychiatric Interview, *BAI* Beck Anxiety Inventory, *MADRS* Montgomery Åsberg Depression Rating Scale, *BMI* Body mass index, *AUDIT* Alcohol Use Disorders Identification Test, *EQ-5D* EuroQoL-5 Dimension Questionnaire, *WAIS-IV* Wechsler Adult Intelligence Scale, 4th edition, *d.s*. digit span, *b.d*. block design, *m.r.* matrix reasoning, *D-KEFS* Delis-Kaplan Executive Function System, *d.f*. design fluency, *S-IGF-1* serum insulin-like growth factor 1, *S-BDNF* serum brain-derived neurotrophic factor, *S-VEGF* serum vascular endothelial growth factor, *CRP* high sensitivity C-reactive protein

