#### Work ability

Patients self-report work ability, weekly number of work hours and if they are on sick-leave in a questionnaire (Additional file 2).

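### If sick leave is analysed as on/off status, the stated Chi-squared rule leaves out the baseline status that the trial collects, at a cost in precision

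*Protocol article*

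**What the plan says.** All references are to the protocol article.

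- **Hypothesis** (Research aims and hypothesis): the main hypothesis is that "an exercise intervention will reduce symptoms of anxiety and the number of days on sick leave". Sick leave is also in the trial's title.
- **Measure** (Work ability): "Patients self-report work ability, weekly number of work hours and if they are on sick-leave in a questionnaire". The questionnaire is Additional file 2, which is not shown.
- **Timing** (Assessments, Table 1): sick leave is marked at T0 (baseline), T1 (12 weeks) and T2 (one year).
- **Rule for categorical data** (Statistical analysis): "For categorical variables, frequencies and percentages will be presented and data analysed using Chi-squared tests".
- **Rule for continuous data** (same paragraph): "continuous data will be analysed using a univariate general linear model (ANCOVA"), followed by "In this model, treatment will be used as a categorical independent variable and baseline levels as covariates".

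The only categorical outcome that the Statistical analysis section names is treatment response, also with Chi-squared tests. No sentence assigns a test to sick leave.

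**The concern.** Read together, the measure, Table 1 and the categorical rule lead to one analysis of a yes/no sick-leave variable: the proportions on leave at T1 or T2 are compared between arms, with no term for who was on leave at T0. Baseline leave status is likely to predict later leave strongly, and the trial holds it for each participant. Continuous outcomes in the same paragraph do get their baseline value.

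Two things are at stake. The first is precision: variation that baseline status would explain is left in the error. The second is the estimate in the trial as it turns out: if one arm happens to start with more people on leave, part of that gap carries through to follow-up and is reported as part of the arm difference. The hypothesis is a reduction in leave, so where patients started matters to the reading of the result.

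**Working it through.** **Inputs from the document.** 60 per arm (Sample size calculation, derived there for the BAI); significance at 0.05, taken as two-sided because sidedness is not stated. The article has no sample size, power or leave rate for sick leave, so there is no figure of its own to reproduce.

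**Assumptions (not in the documents).** p = proportion on leave at baseline; q1 = proportion of these still on leave at follow-up in controls; q0 = proportion of the others newly on leave. Treatment effect: odds ratio 0.3 within each baseline group.

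**Step 1. Baseline-to-follow-up correlation.** With control follow-up proportion c = p·q1 + (1−p)·q0,

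phi = (q1 − q0)·√[p(1−p)] / √[c(1−c)].

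For p = 0.3, q1 = 0.6, q0 = 0.1: c = 0.18 + 0.07 = 0.25, and phi = 0.5 × 0.458 / 0.433 = 0.53.

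**Step 2. Power.** Simulation of two arms of 60 (5,000 trials per row), comparing the Pearson Chi-squared test with a Cochran-Mantel-Haenszel (CMH) test stratified by baseline status:

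| p | q1 | q0 | phi | Chi-squared | CMH | Gain (points) |
|---|---|---|---|---|---|---|
| 0.3 | 0.40 | 0.15 | 0.27 | 56% | 59% | 3 |
| 0.3 | 0.60 | 0.10 | 0.53 | 49% | 59% | 10 |
| 0.3 | 0.75 | 0.07 | 0.70 | 35% | 53% | 18 |
| 0.5 | 0.60 | 0.10 | 0.52 | 63% | 71% | about 9 |

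Hand check of row 2. Odds ratio 0.3 turns 0.60 into 0.310 and 0.10 into 0.032. The treated proportion is 0.3 × 0.310 + 0.7 × 0.032 = 0.116, against 0.25 in controls.

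- Unadjusted: difference 0.134; mean proportion 0.183; SE = √(0.183 × 0.817 × 2/60) = 0.0706; z = 1.90; power about Φ(1.90 − 1.96) = 48%.
- Stratified, with 18 and 42 per arm in the two strata: expected numerator 9 × 0.290 + 21 × 0.068 = 4.03. Variance (18²/35) × 0.455 × 0.545 + (42²/83) × 0.066 × 0.934 = 2.30 + 1.31 = 3.61. z = 4.03/1.90 = 2.12; power about 56%.

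Both are close to the simulated values.

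**Step 3. A second set of assumptions.** Here q1 = 0.70 and q0 = 0.08, both halved by exercise. At p = 20%, 30% and 40%, power is 33%, 45% and 56% with Chi-squared against 44%, 58% and 70% with Mantel-Haenszel. Logistic regression on arm and baseline status gives 45%, 58% and 70%. With weaker persistence (q1 = 0.50, q0 = 0.15, again halved) the gain is only 3 to 4 points.

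**Step 4. Type I error over randomisation.** With no true effect, the Chi-squared test rejects in 4.6% to 5.3% of trials in the Step 2 scenarios. It is not inflated.

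**Step 5. Given a chance imbalance, no true effect.** The baseline difference has SD √[2p(1−p)/60] = √(2 × 0.3 × 0.7/60) = 8.4 points at p = 0.3. A gap of at least 10 points has probability about 23%, and one of at least 20 points about 2%. The expected carry-over is the gap times (q1 − q0), with q1 − q0 = 0.25, 0.50 or 0.68 in the three p = 0.3 rows.

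| On leave at baseline | Expected spurious difference | Chi-squared rejects | CMH rejects |
|---|---|---|---|
| 24/60 vs 18/60 | 2 to 7 points | 5.7–6.2% | about 5% |
| 27/60 vs 15/60 | 5 to 14 points | 9–33% | about 5% |

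**The case against.** The strongest counter-argument is that the Chi-squared route is inferred. The hypothesis counts days, a quantity, and quantities go to the ANCOVA, which does adjust for baseline. The questionnaire is not shown, so days may be recorded as well as status. The general sentence on categorical variables follows a sentence on descriptive statistics, and the one categorical outcome named later is treatment response. This stands as far as the route is concerned: a reader might infer that the trial will definitely test sick leave by Chi-squared, and the document does not say so. It does not remove the point, because the only sick-leave item described in the text is on/off status, and the written rule for such a variable has no baseline term.

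Two other stronger readings are tempting and fail.

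- **That the test is biased or invalid.** Randomisation balances baseline leave in expectation, the unadjusted risk difference is unbiased, and the 5% level holds (Step 4). A baseline gap shows up as an apparent effect only in a trial where such a gap has occurred.
- **That much of the power is lost.** This holds only when baseline and follow-up status are strongly correlated. At a correlation of about 0.27 the loss is 3 points.

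It is also fair to say that the trial was sized on the BAI and makes no power claim for sick leave.

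What a full analysis plan might add is not at issue. The article states a rule, and the point concerns that rule.

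**Conclusion.** The point holds in conditional form. If sick leave is analysed as on/off status, the stated rule discards a baseline value that the trial already collects, while continuous outcomes in the same paragraph keep theirs. The result is a loss of precision in a valid test: about 3 to 18 points of power with 60 per arm across the Step 2 scenarios. Any chance baseline imbalance also stays in the estimate. The size depends on assumed leave rates, effect and persistence, none of which the documents give. The direction was the same in every scenario run.

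The article also leaves open which variable is meant, since the hypothesis is in days and the described item is status. That has to be settled first, because it decides whether the adjusted or the unadjusted rule applies. The change is worth making because it costs almost nothing, not because the planned test would be wrong.

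**What to change.** 1. State which sick-leave variable tests the hypothesis, number of days or on/off status, and bring the hypothesis and the Work ability section into line.
2. Analyse status at T1 and at T2 by logistic regression with arm and baseline status, reporting a standardised risk difference with its 95% confidence interval. A Mantel-Haenszel comparison stratified by baseline status is a simple alternative.
3. If days are collected, analyse them with baseline adjustment too, by a count or rank-based model if the histogram check in the plan fails.
4. Use the same form for other yes/no outcomes with a T0 value, such as psychoactive drug use. Keep frequencies and percentages as description.

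Cost: a sentence or two in the analysis section and one extra model term, with no new data or patients. The article describes the study as ongoing, with final unblinding only after the one-year follow-up, so on the article's timeline the change can be made blind. The small downside is a model-based or stratified estimate in place of a simple table test.

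### The responder outcome is tested without its baseline score: the Chi-squared test is valid, but it can give up power that a baseline-adjusted model would recover at almost no cost

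*Protocol article*

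**What the plan says.** The Statistical analysis section of the protocol article treats the two kinds of outcome differently.

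- Continuous outcomes go into an ANCOVA in which "treatment will be used as a categorical independent variable and baseline levels as covariates".
- For the responder outcome: "The categorical outcome “treatment responsive” will be analysed using Chi-squared tests". No covariate and no particular contrast between arms is named.
- The threshold is common to both: "A p-value below 0.05 will be considered statistically significant for all analyses".
- The section promises intervals for mean changes ("Data will be presented as changes of means with corresponding 95% confidence intervals"). For categorical variables it promises frequencies, percentages and a test.

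The baseline information exists: "Assessments occur at baseline, post-intervention (after 12 weeks) and at one-year follow-up", and Table 1 of that section lists the BAI at all three visits. The article does not say which scale or threshold makes a patient 'treatment responsive'.

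**The concern.** Whether a patient meets a response rule often depends on the starting score. Someone who starts low reaches a final-score cut-off more easily. Someone who starts high has more room for a large absolute fall. Where that dependence is strong, part of the variation in response is predictable from a value already on file. A test that ignores it works with more noise than it needs to.

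The article applies this reasoning to the continuous outcomes but names a method for the responder outcome that leaves it out. Because a method is named, this is more than a detail left for later: a different main analysis would depart from the published plan. At stake is the chance of detecting a real difference in response between the three arms.

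**Working it through.** **1. The plan's own figures.** The article gives no response rate, responder sample size or responder power, so there is no responder figure to reproduce. The only power statement (Sample size calculation) concerns BAI means: 60 per arm, 80% power, 5 points, SD 9. With n = 2(1.96 + 0.84)² × (SD/difference)², 5 points and SD 9 give 51 per arm, and a standardised effect of 0.5 gives 63. Neither is 60, but that is a separate matter. Here I use only 60 per arm, SD 9 and the 5-point effect.

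**2. Assumptions not in the documents.**
- Response is based on the BAI, with baseline mean 22 and control improvement 5 points, so the control follow-up mean is 17.
- The baseline-to-follow-up correlation ρ is 0.3, 0.5 or 0.7. Scores are normal with SD 9 at both visits.
- Effects for control/low/high are 0/2.5/5 (ordered) or 0/5/5 (both exercise arms equal).
- Three illustrative rules: final score below 12, fall of at least 10 points, fall of at least 50%.
- Tests are two-sided at 5%.

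**3. Check on the inputs.** For the final-score rule the response rates are Φ((12 − 17)/9) = 0.289, Φ((12 − 14.5)/9) = 0.391 and Φ((12 − 12)/9) = 0.500, with mean 0.393. The noncentrality of the three-arm Chi-squared test is 60 × [(0.289 − 0.393)² + (0.391 − 0.393)² + (0.500 − 0.393)²] / (0.393 × 0.607) ≈ 5.6. On 2 df that is about 55% power, close to the simulated 56 to 59% below.

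**4. How strongly each rule depends on baseline.** Write the score behind the rule as follow-up minus k × baseline, with k = 0 (cut-off), 1 (absolute fall) or 0.5 (50% reduction). Its correlation with baseline is (ρ − k)/√(1 + k² − 2kρ). For ρ = 0.3/0.5/0.7:
- cut-off: 0.30 / 0.50 / 0.70
- absolute fall: −0.59 / −0.50 / −0.39
- 50% reduction: −0.21 / 0.00 / 0.27

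The first two rules leave baseline something to explain. The third leaves little, and nothing at ρ = 0.5.

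**5. Simulated power.** Each setting has 4,000 trials. Each cell shows the three-arm Chi-squared test → the 2-df logistic test adjusted for baseline, in %, with the change in points in brackets.

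| Rule | Effects | ρ = 0.3 | ρ = 0.5 | ρ = 0.7 |
|---|---|---|---|---|
| Final score below 12 | 0/2.5/5 | 56.3 → 59.1 (+2.8) | 58.5 → 65.6 (+7.1) | 55.7 → 73.4 (+17.7) |
| Final score below 12 | 0/5/5 | 68.2 → 72.0 (+3.8) | 67.8 → 76.9 (+9.1) | 68.4 → 86.8 (+18.4) |
| Fall of at least 10 | 0/2.5/5 | 41.9 → 53.5 (+11.6) | 54.2 → 62.8 (+8.6) | 79.5 → 82.8 (+3.3) |
| Fall of at least 10 | 0/5/5 | 52.5 → 64.7 (+12.2) | 68.7 → 77.9 (+9.2) | 88.7 → 91.5 (+2.8) |
| Fall of at least 50% | 0/2.5/5 | 57.1 → 58.6 (+1.5) | 66.3 → 66.0 (−0.3) | 79.2 → 81.8 (+2.6) |
| Fall of at least 50% | 0/5/5 | 70.6 → 72.8 (+2.2) | 79.3 → 79.9 (+0.6) | 90.3 → 91.6 (+1.3) |

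The simulation error of one power figure is about √(0.66 × 0.34/4000) = 0.7 points, so −0.3 is no change. A separate run of the same setup puts the lower end for the first two rules at about +2.

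**6. Validity.** With no effect in any arm and ρ = 0.5, Chi-squared rejects in 5.0 to 5.4% of trials and the adjusted test in 5.3 to 5.5%.

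**7. High versus low.** With effects 0/2.5/5 and ρ of 0.5 to 0.6 (1,000 runs per setting, four rules), the pairwise Chi-squared test has 21 to 33% power and the adjusted model 25 to 32%, a difference of about 0 to +4 points.

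**The case against.** The strongest reply is that nothing here is wrong. Randomisation makes the Chi-squared test valid, and its error rate already allows for chance baseline imbalance. The responder outcome is not called primary and does not drive the sample size, and the BAI itself has a baseline-adjusted analysis. The response rule is undefined and nothing ties it to the BAI: the M.I.N.I. and MADRS are also recorded at every visit. Under a 50% rule the gain is negligible. All of this stands, and it limits the point to efficiency with a conditional size. It does not remove the point, because no rule tried showed a material loss from adjusting.

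Some stronger readings are tempting but are not supported.

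- *Baseline anxiety enters every continuous model.* The wording on baseline levels most naturally means each outcome's own baseline value.
- *The Chi-squared test is specially at fault for the hypothesis that* "the effect will be larger for high-intensity exercise than for low-intensity". The article does not assign that hypothesis to the responder outcome, and dose-response is a secondary aim. The plural 'tests' can include a pairwise high-versus-low comparison, and the ANCOVA also enters arm as an unordered category.
- *No effect size will be available.* Frequencies and percentages are promised, and risk differences follow from them.
- *Any disagreement with the ANCOVA would come from imbalance alone.* Dichotomising can produce disagreement by itself, and adjustment does not prevent that.

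**Conclusion.** The point holds as a modest weakness of efficiency and specification. The stated responder test leaves out a baseline score that the trial collects, while the continuous outcomes in the same paragraph are adjusted for theirs. With the document's 60 per arm and SD 9, adjustment changes three-arm power by about +2 to +18 points for an absolute-fall or cut-off rule and by about 0 to +3 for a 50% reduction. These ranges rest on the assumed baseline mean, control improvement, correlations, effect patterns and a BAI-based rule. The documents alone cannot narrow them.

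A reader might infer that the planned test is biased, or that adjustment would make the responder outcome able to settle high against low intensity. Neither follows: type I error is kept, and power for that comparison stays at roughly a quarter to a third either way.

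**What to change.** Make the main responder analysis a logistic regression with arm as a three-level factor and, as covariate, the baseline score of the scale that defines response (baseline BAI if response is BAI-based). Report low versus control, high versus control and high versus low, preferably as standardised risk differences and otherwise as odds ratios, each with a 95% confidence interval. Keep the Chi-squared test as a supporting check. Make the change before the final unblinding that the Blinding section sets for June 2021, and present high versus low as an estimate with its interval, given its low power.

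The cost is one sentence in the analysis section and a few lines of SAS, with no new data. The one drawback is that an odds ratio from this model is conditional on baseline; a standardised risk difference avoids that.

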## Methods/design

### Study design

This is a randomized, parallel, controlled superiority clinical intervention study with three assessment points (baseline, post-intervention and one-year follow-up). The study is ongoing and was registered under ClinicalTrial.gov NCT03247270 on August 8, 2017 (https://clinicaltrials.gov/ct2/show/NCT03247270). The protocol was prepared in accordance with the SPIRIT 2013 statement. [29] Participants are randomly assigned to an exercise program of one low-intensity training group, one moderate- to high intensity training group and one control non-exercise group, with 1:1:1 allocation. Assessments and interventions are conducted at Primary Care Rehab (Närhälsan Primary Care) in Gothenburg, Sweden. Figure 1 shows the study design of the trial.

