### Sample size calculation/power calculation

A power analysis was performed by a statistician prior to study initiation. We have calculated, based on other studies [41, 42], that an effect size of 0.5 difference between the groups is clinically relevant, which equates to a 5-point difference between the groups on the BAI scale. Standard deviations from a previous study using BAI as the outcome measurement were in the interval of 5–10 [43]. We use SD 9 for our calculations. Based on these assumptions, we should include 60 patients in each of the treatment arms to reach 80% power at the 5% significance level. In order to achieve an adequate number of study participants, we will initially recruit 25% more subjects than required.

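### A flat 0.05 threshold for every analysis, set against a primary aim of five unranked outcome domains, three arms and two follow-ups, leaves the false-positive risk of the primary aim uncontrolled

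*Protocol article*

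**What the plan says.** The decision rule in the Statistical analysis section is one sentence: "A p-value below 0.05 will be considered statistically significant for all analyses". The article gives no adjustment, testing order or gatekeeping step. The model is an ANCOVA with treatment as a categorical factor and the baseline value as covariate, reported with p-values for group comparisons. It is not said whether these come from the overall treatment test, from contrasts with control, or from all pairs of arms.

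Research aims and hypothesis gives the primary aim as the "effects of an exercise intervention on anxiety symptoms, cognitive function, physical health and quality of life and work ability". The main hypothesis joins anxiety, sick leave, cognition and physical health. An additional hypothesis expects a larger effect at high than at low intensity.

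Study design describes a superiority trial with two exercise arms and "one control non-exercise group, with 1:1:1 allocation", assessed at baseline, after the intervention and at one year. Table 1 lists several measures for some domains; cognition alone has three WAIS-IV subtests and one from D-KEFS.

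The BAI stands out only in the sample size section: "an effect size of 0.5 difference between the groups is clinically relevant", "which equates to a 5-point difference between the groups on the BAI scale", "We use SD 9 for our calculations", and hence "we should include 60 patients in each of the treatment arms to reach 80% power at the 5% significance level". No time point is attached to that calculation.

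**The concern.** A superiority claim needs a stated error rate. Here the threshold is fixed, but the set of tests that may support the primary aim is not. Five domains share the rank of primary, at two time points and with up to three comparisons each, and each result is called significant at 0.05. A report could then present a significant result in one domain, at one time, for one comparison as support for the primary aim, and a reader could not say how likely that was under no effect. The sample size does not help, because it uses the full 5% level on the BAI alone.

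This is more than a detail left out of a condensed article. The sentence is a positive rule covering all analyses, so a later plan with a hierarchy would have to depart from it.

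**Working it through.** **The plan's own figure.** Inputs: 5 points, SD 9, 80% power, 5% level (two-sided assumed).

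- Per arm, n = 2 × (1.960 + 0.842)² × (9/5)² = 51. With the stated effect size of 0.5 (SD 10) it is 63.
- At 60 per arm the power of one pairwise test is Φ(5 / (9 × √(2/60)) − 1.960) = Φ(3.043 − 1.960) = 86.1% for SD 9, and 78.2% for SD 10.

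So 60 does not follow from SD 9, and the article does not say which test was powered. That is a separate matter. What counts here is that no allowance for several outcomes, times or comparisons is described.

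**Independent tests.** With k tests at 0.05 the chance of at least one false positive is 1 − 0.95^k: 14.3% for k = 3, 22.6% for 5, 40.1% for 10, and 78.5% for 30 (5 domains × 2 times × 3 comparisons). These overstate the risk, because the comparisons share arms and the outcomes are correlated.

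**Allowing for correlation.** This is a simulation under no effect anywhere: three equal arms, one measure per domain, 100,000 runs. The documents give no correlations. They are assumed as 0 to 0.9 between domains and 0.5 or 0.8 between times.

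| Tests counted | Overall test only | Two contrasts with control | Three pairwise |
|---|---|---|---|
| BAI, one time | 5% | 9% | 12% |
| BAI, both times | 8–9% | 14–16% | 18–22% |
| Five domains, one time | 10–23% | 18–38% | 23–48% |
| Five domains, both times | 16–38% | 26–58% | 33–70% |

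At a between-domain correlation of 0.5, the last row is 28–32%, 44–50% and 54–60%.

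**The remedy checked.** With three arms, any two pairwise equalities imply that all three arms are equal. Testing the 2-df treatment effect at 0.05, and then each pair at 0.05 only if it is significant, is therefore a closed procedure. Its simulated familywise error with all arms equal is 5.0%.

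The overall test has noncentrality n × Σ(μ − μ̄)² / SD². At 60 per arm and SD 9:

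- True differences from control of 0/5/5 (control, low, high): 60 × 16.67 / 81 = 12.35, power 88.7%.
- True differences 0/2.5/5: 60 × 12.5 / 81 = 9.26, power 77.6%.

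Power for high intensity against control, by simulation:

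| Pattern, SD 9 | Unadjusted | Closed procedure | Bonferroni for three |
|---|---|---|---|
| 0/5/5 | 86% | about 83% | 73% |
| 0/2.5/5 | 86% | about 77% | 73% |

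At SD 10 and pattern 0/2.5/5 the figures are 78%, 67% and 63%.

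**The case against.** Four points on the other side deserve weight.

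- **The hypothesis is joint.** A reader might infer that any one of dozens of significant tests would confirm the main hypothesis. The article does not say so. Its parts are joined by conjunction, and a rule requiring all of them to succeed would not inflate the error. But the article does not state that rule either, and it would still need one time point and one comparison fixed per domain. The 0.05 sentence labels p-values; it defines no success criterion.
- **The number of tests is open.** A reader might count ten outcomes and three pairwise tests each, which gives 56–66% at one time point (between-outcome correlation 0.5–0.3). The article gives no count of ten and does not prescribe three unadjusted pairwise tests. The same ten outcomes give 46–55% with two control contrasts and 29–36% with the overall test. High against low intensity belongs to an additional hypothesis and a secondary aim, so the two-contrast column may fit the main hypothesis better. All of this stands, and is why ranges are given.
- **A fuller plan may settle it.** Naming the primary outcome and handling multiplicity are often left to an analysis plan, and a 0.05 threshold can be applied to adjusted p-values. That is fair for the silence on a primary outcome. It does not remove the stated rule, which as worded draws no line between primary and other analyses.
- **Twelve weeks is not fixed by the power calculation.** The sample size section names no time point, and Project timeline puts primary completion at June 2021, the month that Blinding gives for the end of the one-year follow-up. The choice remains the sponsor's.

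**Conclusion.** The concern holds in limited form. The stated rule does not control the error of the primary aim unless success is required in every domain, or unless one BAI analysis at one time point, led by the overall test, is the sole primary analysis. The article says neither. For five domains at two times, the lowest figure found is 16%, with only overall tests and a between-domain correlation of 0.9. The highest is 70%, with three pairwise tests and uncorrelated domains. These figures rest on assumed correlations and one measure per domain; Table 1 lists more than one for some domains.

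The documents do not show that the investigators would claim success on a single positive test, so no one percentage is the trial's false-positive rate. What is shown is that the rule leaves the rate undefined and, on most readings, well above 5%.

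**What to change.** Before unblinding:

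1. Name the BAI, the outcome used in the power calculation, as the single primary outcome at one declared time point. The sponsor must choose it; 12 weeks, the end of the intervention, is one natural choice.
2. Test the 2-df ANCOVA treatment effect at 0.05. Only if it is significant, test the three pairwise contrasts, each at 0.05.
3. Limit the 0.05 sentence to this family.
4. Report the other domains, the other time point and the subgroups as secondary or exploratory, with 95% confidence intervals and no confirmatory claim.

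This changes wording only and needs no extra patients. The Blinding section places final unblinding after the one-year follow-up, so the change can be made credibly until then.

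The cost is some power. Against an unadjusted test of high intensity versus control, the loss is about 3 points if both exercise arms work equally and about 9 points under a graded effect (SD 9, 60 per arm). In the graded case, which is the one the trial's additional hypothesis expects, the closed procedure recovers only about 4 of the 13 points that Bonferroni would cost. Significance in the other domains would also no longer count as confirmation.
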